## Abstract

**Background:**

High-risk subsolid pulmonary nodules, especially mixed ground-glass nodules, can represent precancerous or early-stage lung adenocarcinoma spectrum lesions. Standard management relies mainly on risk stratification, repeated thin-slice computed tomography, and invasive diagnosis or surgery when progression suggests malignancy. Safe adjunctive pharmacologic options to reduce nodule progression remain limited. Yifei Sanjie Pill (YFSJ) is an 8-herb traditional Chinese medicine formula that has been previously studied as an adjunctive treatment for non–small cell lung cancer. However, its effect on high-risk pulmonary nodules—a distinct clinical condition—has not yet been investigated.

**Objective:**

This protocol describes a multicenter randomized trial evaluating the efficacy, safety, and exploratory mechanisms of YFSJ for preventing high-risk pulmonary nodule progression.

**Methods:**

Adults aged 18 to 80 years with single or multiple mixed ground-glass nodules measuring ≤8 mm will be randomized in a 1:1 ratio to receive YFSJ optimized formula granules or matched placebo granules, 2 packets twice daily for 6 months. Both groups will receive guideline-based computed tomography surveillance and any clinically indicated standard diagnostic or therapeutic care. The primary outcome is the 2-year pulmonary nodule progression rate, defined as an increase in the lesion’s longest diameter of ≥2 mm, an increase in the solid component of ≥1 mm, or the appearance of a new solid component. Secondary outcomes include lung cancer detection rate, surgery rate, 6-month nodule size and volume change, artificial intelligence–based malignancy risk index, traditional Chinese medicine symptom score, Hospital Anxiety and Depression Scale (HADS) score, Pittsburgh Sleep Quality Index (PSQI) score, safety indicators, and exploratory plasma biomarkers. The primary analysis will use the full analysis set, Kaplan-Meier estimates, log-rank testing, and Cox regression adjusted for center and key covariates; repeated outcomes will be analyzed using mixed-effects models.

**Results:**

The study was funded in 2022 and approved by the Research Ethics Committee of the First Affiliated Hospital of Guangzhou University of Chinese Medicine (K-2022‐131-XZ-01). Recruitment started in June 2023 and was scheduled for completion in December 2025. As of April 2026, a total of 589 participants have completed randomization. The final 2-year follow-up is scheduled for December 2027. Database lock and primary analysis are planned for early 2028, and submission of the first results is expected in spring or summer 2028.

**Conclusions:**

This trial will determine whether adding YFSJ to guideline-based surveillance can reduce high-risk pulmonary nodule progression and provide mechanistic evidence for integrative early lung cancer prevention.

## Introduction

Lung cancer remains a major cancer burden in China. National mortality surveillance data showed that cancer-related deaths in China reached 2,397,772 in 2020, a 21.6% increase compared with 2005, and that tracheal, bronchial, and lung cancers remained among the leading causes of cancer mortality [1]. Because prognosis depends strongly on stage, strategies that identify and manage early lung cancer spectrum lesions are essential.

The broader use of low-dose computed tomography (CT) has increased the detection of pulmonary nodules, including pure ground-glass nodules and mixed ground-glass nodules [2-4]. Most small nodules are benign or indolent, but persistent subsolid nodules may correspond to atypical adenomatous hyperplasia, adenocarcinoma in situ, minimally invasive adenocarcinoma, or invasive adenocarcinoma. The National Comprehensive Cancer Network (NCCN) and Fleischner Society lung nodule surveillance guidelines emphasize risk-adapted surveillance, avoidance of unnecessary invasive procedures, and timely intervention when growth or the development of a solid component increases the likelihood of malignancy [5,6].

The target population in this study is adults with high-risk pulmonary nodules rather than patients with confirmed advanced lung cancer. For nodules ≤8 mm, immediate resection may overtreat indolent disease, whereas surveillance alone does not actively address biological progression. Long-term follow-up studies also indicate that some ground-glass nodules may grow after prolonged stability, supporting the need to investigate safe interventions that can be used alongside guideline-based CT surveillance [7].

Artificial intelligence (AI)–assisted CT analysis is increasingly used to quantify pulmonary nodule size, volume, density, morphology, and malignancy probability. Recent studies have shown that AI and data-driven risk stratification can support risk classification and may outperform size-only approaches in selected settings [8,9]. In this trial, AI-derived nodule volume and malignancy risk index are included as secondary imaging outcomes to provide quantitative and reproducible assessments in addition to conventional radiologist interpretation.

Psychological distress is not the primary target of this trial, but it is clinically relevant for patients who undergo repeated surveillance for indeterminate pulmonary nodules. Previous studies have reported anxiety, depression, sleep disturbance, and reduced quality of life in patients with pulmonary nodules [10,11]. Therefore, the Hospital Anxiety and Depression Scale (HADS) and Pittsburgh Sleep Quality Index (PSQI) are included as secondary patient-reported outcomes, whereas the primary end point remains objective nodule progression.

Traditional Chinese medicine (TCM) is widely used in China as part of integrative oncology care. Network pharmacology and experimental studies suggest that TCM formulas may influence multiple pathways involved in pulmonary nodule and early lung cancer biology, including inflammation, cell proliferation, apoptosis, immune regulation, and tumor microenvironment remodeling [12,13]. These multitarget effects provide a biological rationale for evaluating TCM as an adjunct to surveillance in high-risk pulmonary nodules, provided that rigorous randomized evidence is generated.

Yifei Sanjie Pill (YFSJ), also referred to as the Yi-Fei-San-Jie formula, is an 8-herb formula developed from the clinical experience of [name]. Prior studies have evaluated YFSJ as an adjunctive treatment for non–small cell lung cancer [14-16], but this study investigates a different clinical population: patients with high-risk pulmonary nodules. The source formula contains *Sarcandra glabra*, Bombyx batryticatus, *Ranunculus ternatus*, *Iphigenia indica*, Bulbus *Fritillariae thunbergii*, *Pinellia ternata*, *Ganoderma lucidum*, and *Panax quinquefolius* [17]. Recent mechanistic works have identified bioactive components, such as ginsenosides, peimisine, and peimine, and have suggested regulation of transforming growth factor-β signaling, tumor immune escape, deoxycholic acid metabolism, and the TGR5/STAT3/PD-L1 (Takeda G protein-coupled receptor 5, signal transducer and activator of transcription 3, and programmed death-ligand 1) axis [17,18]. These findings support the plausibility of YFSJ in modulating early lung cancer–related biology, but they do not establish efficacy in preventing pulmonary nodule progression.

The purpose of this multicenter, randomized, double-blind, and placebo-controlled trial is to evaluate whether YFSJ, administered for 6 months in addition to guideline-based surveillance, reduces the 2-year progression rate of high-risk pulmonary nodules compared with placebo plus the same surveillance strategy. We hypothesize that YFSJ will reduce nodule progression without increasing clinically meaningful adverse events and will improve selected TCM symptoms, psychological distress, sleep quality, and exploratory plasma biomarkers related to phlegm-heat-toxin pathogenesis.

## Methods

### Study Governance

The research team for this study includes experts from institutions such as Guangzhou University of Chinese Medicine and Nanjing University of Chinese Medicine, with defined roles such as principal investigator and study coordinators responsible for data collection, patient management, and analysis. The trial sponsor, Guangzhou University of Chinese Medicine First Affiliated Hospital, oversees the design, management, data analysis, and interpretation of the trial, including the publication of results. The coordinating center for the trial, also located at Guangzhou University of Chinese Medicine First Affiliated Hospital, ensures the trial’s overall operation, managing data collection, patient follow-up, and protocol compliance in collaboration with various teams. Contact information for the principal investigators and coordinators is provided to facilitate clear communication. This study protocol was developed in accordance with the SPIRIT (Standard Protocol Items: Recommendations for Interventional Trials) 2013 Statement. The completed SPIRIT checklist is provided in Checklist 1.

### Ethical Considerations

The clinical trial protocol (version 3.0, March 20, 2023) was approved by the Research Ethics Committee of the First Affiliated Hospital of Guangzhou University of Chinese Medicine (approval number: K-2022‐131-XZ-01). The trial is registered in the Chinese Clinical Trial Registry (ChiCTR2300069570) and will be conducted in accordance with the Declaration of Helsinki and Good Clinical Practice principles.

Written informed consent will be obtained before any trial-specific procedures. Investigators will explain the study’s purpose, interventions, expected benefits, foreseeable risks, alternative management options, confidentiality protections, voluntary participation, and the right to withdraw without affecting usual medical care. Additional consent will be obtained for the storage and exploratory analysis of plasma samples.

Participant data will be entered into an electronic data capture (EDC) system using coded study identifiers. Direct identifiers will be stored separately from research data, access will be restricted to authorized study personnel, and analyses will use deidentified datasets. Biological samples will be labeled with coded identifiers and used only for approved analyses described in the protocol or subsequent ethics-approved amendments.

Participants will not be denied clinically indicated diagnostic evaluations or standard treatments. Study medication and protocol-specified assessments will be provided by the study. No direct financial incentives are planned. Medical management and compensation for trial-related injuries will be provided according to institutional and national regulations.

### Case Selection

#### Sample Size Estimation

This trial uses the 2-year disease progression rate of pulmonary nodules as the primary end point. Previous studies have reported a 2-year progression rate of ≤8 mm mixed ground-glass nodules at approximately 24% [19]. Assuming a 2-year progression rate of 14% in the intervention group, with 80% power, a 5% false-positive error rate (2-sided), and a dropout rate controlled within 20%, a total of 596 participants need to be enrolled. The trial will include 600 patients, with 300 in the experimental group and 300 in the control group (Figure 1).

**Figure 1. F1:**
[figure not shown]
Clinical study flowchart. CT: computed tomography; TCM: traditional Chinese medicine; YFSJ: Yifei Sanjie Pill.

#### Inclusion Criteria

Participants will be eligible for enrollment in the study if they meet all of the following inclusion criteria:

Age 18 to 80 years, regardless of gender≤8 mm mixed ground-glass pulmonary nodule, single or multiple (with the largest lesion ≤8 mm)No major organ dysfunction, normal blood routine, liver, kidney, and heart functionsSigned informed consent and willingness to undergo treatment and follow-up

#### Exclusion Criteria

Participants meeting any of the following criteria will be excluded from the study:

Patients with stage III-IV malignant tumors or patients with stage I-II malignant tumors who cannot rule out metastasis of pulmonary nodules postoperativelyAcute respiratory diseases or pulmonary diseases that interfere with diagnosis, such as acute pneumonia, acute bronchitis, silicosis, and tuberculosisPatients with severe primary heart, liver, kidney, hematological, or other serious diseases affecting survivalPatients with clinically significant immune disease, autoimmune disease, immunodeficiency, or current systemic immunosuppressive or immunomodulatory treatment that could affect safety assessments or immune-related outcomesPatients with severe depression, mania, obsessive-compulsive disorder, or schizophreniaAllergy to the TCM components used in this studyPatients who have participated in other drug clinical trials in the past 3 months or are currently participating in other drug clinical trialsPregnant or lactating patients, as well as women of childbearing age with pregnancy plans within 1 year

#### Termination or Withdrawal Criteria

Participants will be withdrawn from the study or have their treatment discontinued if any of the following conditions occur:

Patients experiencing severe adverse events (life-threatening or significantly impacting normal daily work and life) will discontinue treatmentPatients experiencing severe and persistent allergic reactions will cease treatment and be considered ineffective casesPatients unwilling or unable to continue clinical trials for any reason and requesting withdrawalPatients who undergo other treatments, such as surgery, without disease progression will be considered censored casesSignificant protocol violations (adherence <80% or >120%)

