#### Dropout Criteria

All participants who signed the informed consent and were eligible for observation but did not complete the observation period for any reason will be considered dropouts.

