### Follow-Up and Data Collection

Baseline data will include demographics, smoking history, comorbidities, prior cancer history, medication history, physical examination, vital signs, blood routine, liver function, kidney function, urinalysis, stool examination, tumor markers, ECG, chest CT, AI-derived nodule variables, TCM symptom score, HADS, and PSQI. Follow-up visits will occur at 3 and 6 months during the intervention period and every 6 months thereafter until nodule progression, surgery, withdrawal, death, loss to follow-up, or study completion. The trial protocol is version 3.0 (March 20, 2023), and the schedule of study procedures is shown in Table 2.

**Table 2. T2:** Schedule of study procedures, assessments, and follow-up visits.

Procedure	Screening/baseline	Randomization	Month 3	Month 6	Month 12	Month 18	Month 24/ end point
Eligibility	✓						
Consent	✓						
Demog.^a^	✓						
Random.^b^		✓					
Study drug		Start	Continue	End			
Meds^c^	✓	✓	✓	✓	✓	✓	✓
Vitals or AEs^d^	✓		✓	✓	✓	✓	✓
Labs or ECG^e^	✓		✓	✓	As indicated	As indicated	✓
CT^f^	✓			✓	✓	✓	✓
AI^g^	✓			✓	✓	✓	✓
TCM^h^ symptoms	✓		✓	✓	✓	✓	✓
HADS^i^ or PSQI^j^	✓		✓	✓	✓	✓	✓
Plasma	✓			✓			Optional or if specified
End point							✓

a Demog.: demographics and medical history.

b Random.: randomization and dispensing.

c Meds: concomitant medication review.

d AEs: adverse events.

e ECG: electrocardiogram.

f CT: computed tomography.

g AI: artificial intelligence.

h TCM: traditional Chinese medicine.

i HADS: Hospital Anxiety and Depression Scale.

j PSQI: Pittsburgh Sleep Quality Index.

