### Adherence and Retention Strategies

Participants will receive phone reminders before scheduled visits. Participants who miss a visit will be contacted by phone, text message, or home visit, as appropriate, to determine the reason and encourage continued participation. Medication adherence will be assessed through returned packet counts and participant report. Available imaging, laboratory, and questionnaire data will be collected at withdrawal whenever consent permits.

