### Statistical Analysis

Data will be collected at baseline and during follow-up visits using standardized CRFs. Key data include demographics, clinical history, imaging findings (chest CT and AI-assessed nodule features), laboratory results (tumor markers, blood, urine, stool, liver and kidney function, and ECG tests), and patient-reported outcomes (TCM symptom scale, provided in Multimedia Appendix 1, HADS, and PSQI). To ensure data quality, assessors will receive uniform training, and duplicate measurements will be conducted where appropriate. All instruments used have been validated in prior clinical practice. Data collection forms are included in the protocol and managed through an EDC system.

Based on the actual number of participants enrolled in the 2 groups, dropout and exclusion cases, as well as demographic and other baseline characteristics, corresponding efficacy and safety analyses will be conducted. Descriptive statistical analysis will be used, with qualitative indicators described as frequency tables, percentages, or proportions; quantitative indicators will be described as mean (SD), median (IQR), and minimum and maximum values.

For primary end points and clinical efficacy analysis, the main and sensitivity analyses will be performed according to the full analysis set and per-protocol set, respectively. Safety analysis will be conducted using the safety set. The main analysis of the primary end point will use the log-rank test to compare the 2-year progression rates between groups, with Cox regression adjusting for covariates (eg, center) as a sensitivity analysis. Subgroup analyses will be conducted based on the center and whether >8 mm nodules were surgically removed. The malignancy risk index, quality-of-life scores at different time points, and other multiple measurement indicators will be analyzed using mixed-effects models. Eligibility-related protocol deviations, including any deviations from the retained immune disease exclusion criterion, will be documented. Participants with major eligibility deviations will be handled according to the prespecified analysis-set definitions, with sensitivity analysis based on the per-protocol set. Safety end points will summarize adverse reactions and events occurring during the study and compare rates between groups. Hypothesis testing will uniformly use 2-sided tests, providing test statistics and corresponding *P* values, with *P*<.05 considered statistically significant.

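### The withdrawal criteria allow sites to end CT follow-up for poor adherence; adherence should define only the per-protocol set

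*Protocol article*

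**What the plan says.** - **Protocol article, Termination or Withdrawal Criteria.** The lead-in reads "Participants will be withdrawn from the study or have their treatment discontinued if any of the following conditions occur". The items on severe adverse events and severe allergy name a stop of treatment. One item covers participants who ask to leave, and one classes surgery or other treatment without progression as censoring. The last item, adherence below 80% or above 120%, names no action of its own.
- **Dropout Criteria.** Eligible, consented participants who "did not complete the observation period for any reason will be considered dropouts".
- **Sample Size Estimation.** The plan allows for "a dropout rate controlled within 20" percent.
- **Follow-Up and Data Collection.** "Follow-up visits will occur at 3 and 6 months during the intervention period", and then "every 6 months thereafter until nodule progression, surgery, withdrawal, death, loss to follow-up, or study completion". Table 2 ends study drug at month 6 and schedules follow-up CTs at months 6, 12, 18 and 24.
- **Adherence and Retention Strategies.** Staff contact participants who miss visits. For those who leave, "Available imaging, laboratory, and questionnaire data will be collected at withdrawal whenever consent permits".
- **Statistical Analysis.** "The main analysis of the primary end point will use the log-rank test to compare the 2-year progression rates between groups". On analysis sets, "the main and sensitivity analyses will be performed according to the full analysis set and per-protocol set, respectively".

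**The concern.** Adherence is a behaviour after randomization. The treatment itself can influence it, for example through tolerability, and it may be related to prognosis. It is a reasonable criterion for a per-protocol set but a poor reason to stop measuring the outcome.

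Dosing lasts 6 months and the endpoint is read over 24. If a participant is withdrawn at month 6 because the packet count was too low or too high, only one of the four follow-up CTs exists. The full analysis set can keep that person, but only as someone censored at month 6. Censoring then depends on adherence, and the main analysis drifts toward the per-protocol comparison that the plan reserves for sensitivity. No later analysis decision can restore a scan that was not taken. The issue is validity; no loss of power is claimed.

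**Working it through.** **1. The rule, read across sections.**

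| Question | What the article provides |
|---|---|
| What follows from adherence outside 80% to 120%? | Study withdrawal or treatment stop; the item does not choose |
| When is adherence judged? | Not stated; returned packets and participant report |
| What is left to stop at month 3? | Study drug, so a treatment stop is possible and need lose no outcome data |
| What is left to stop at month 6? | No study drug; a treatment stop has no object |
| What does withdrawal do? | Ends the visits; available data are collected at that point |
| Is there a statement that poor adherers keep having trial CTs? | None in the article |

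Withdrawal at month 6 would lose 3 of 4 follow-up CTs, covering 18 of 24 months.

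**2. The plan's own figure.** Inputs from Sample Size Estimation: 24% and 14% at 2 years, 80% power, two-sided 5%, 20% dropout.

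- Unpooled variance: 0.24×0.76 + 0.14×0.86 = 0.3028.
- Per arm: 0.3028 × (1.960 + 0.842)² / 0.10² = 237.7, so 238.
- With dropout: 238 / 0.8 = 297.5, so 298. Total 596, as stated.

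By the dropout definition, people withdrawn for adherence count against the 20% allowance (0.20 × 600 = 120). If they fit within it, power does not drop below plan.

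**3. Share of events after month 6.** Assuming constant hazards, S(t) = (1 − p)^(t/24).

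- Control: 1 − 0.76^0.25 = 6.63 points by month 6; 17.37 of 24 later (72%).
- YFSJ: 1 − 0.86^0.25 = 3.70 points by month 6; 10.30 of 14 later (74%).

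**4. Illustration of bias.** The article gives no adherence rates, so the share s of poor adherers and their 2-year risk pp are assumptions. I stop at s = 20% of an arm (60 people). Adherers have risk pa, and every poor adherer is assumed censored at month 6.

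- With full follow-up: rate = (1 − s)·pa + s·pp.
- Kaplan-Meier with censoring: 1 − [(1 − s)·Sa(6) + s·Sp(6)] · Sa(24)/Sa(6).

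Worked example: YFSJ only, pa = 14%, pp = 24%, s = 0.2. Kaplan-Meier gives 1 − [0.8×0.9630 + 0.2×0.9337] × 0.8930 = 14.52%, so the difference is 24 − 14.52 = 9.48 points. With full follow-up the rate is 16% and the difference 8.00.

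| Scenario | s | Difference with censoring | Difference with full follow-up | Shift (points) |
|---|---|---|---|---|
| (a) YFSJ only, poor adherers get no benefit (24%) | 10% / 20% | 9.74 / 9.48 | 9.00 / 8.00 | +0.74 / +1.48 |
| (a') YFSJ only, half benefit (19%) | 10% / 20% | 9.87 / 9.74 | 9.50 / 9.00 | +0.37 / +0.74 |
| (b) Placebo only, poor adherers at 30%, arm average held at 24% | 10% / 20% | 9.51 / 8.89 | 10 / 10 | -0.49 / -1.11 |
| (c) Both arms, poor adherers at 1.25 times the arm average (30% and 17.5%) | 20% | 9.54 | 10 | -0.46 |
| (d) Poor adherers at the same risk as the rest of their arm | any | 10 | 10 | 0 |

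In (c) the hazard ratio, ln(1 − YFSJ rate)/ln(1 − control rate), is 0.551 against 0.550. A simulation that detects progression only on the 6-month CT grid agrees closely: 9.72 / 9.46 for (a), 9.89 / 9.75 for (a') and 9.48 / 8.88 for (b).

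For scale, with 240 evaluable per arm the standard error of the difference is √(0.3028/240) = 3.6 points.

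**The case against.** **Withdrawal is not required.** A reader might infer that, once dosing is over, withdrawal is the only action left and poor adherers must leave the trial at month 6. The text does not support this. The lead-in offers two actions, and a criterion meant to stop treatment can simply lapse when there is no treatment. The severe-adverse-event item would be read that way after month 6. What stands is that the text permits withdrawal for adherence, and nothing in the article rules it out.

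**The article condenses protocol version 3.0.** The full document may attach an action to each item. That is possible, and if so the clarification is already made. But the point rests on a stated rule for managing participants, together with a stated rule that withdrawal ends visits.

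**Other provisions soften the loss.** Guideline-based CT surveillance runs in both arms as usual care, staff pursue missed visits, and the full analysis set is primary. This is true and makes repair easier. Even so, the article does not say that scans after withdrawal are collected for the trial, and the analysis set can use only scans it has.

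**The figures are assumed and small.** This largely stands. The ends of the range need poor adherence in one arm only, which a matched, blinded placebo makes less likely, and every case withdrawn at month 6. They amount to about 0.3 and 0.4 of a standard error (1.11/3.6 and 1.48/3.6). Scenario (a) also presupposes a true effect: if YFSJ does nothing and poor adherers share the common risk, its bias vanishes. The range should not be read as an estimate of the bias in this trial.

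**Conclusion.** The point holds in limited form, as a cheap improvement. The withdrawal criteria leave the consequence of poor adherence open between stopping treatment and leaving the study. Because leaving the study ends visits, sites may read the text as allowing CT follow-up to end for that reason.

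If that happens at month 6, three of four follow-up CTs are lost, over the period that holds nearly three quarters of expected progressions under constant hazards at the planned rates. Censoring in the primary log-rank comparison is then informative if poor adherers differ in risk from others in their arm. The comparison is biased mainly when the share of poor adherers, or their excess risk, differs between arms. The direction cannot be fixed in advance. For adherence above 120% no reduced benefit is assumed; those participants lose the same scans, with bias only if their risk differs.

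The documents do not show that anyone has been withdrawn for adherence, that the primary result will be materially biased, or that power falls below plan.

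**What to change.** 1. Remove adherence below 80% or above 120% as a reason for study withdrawal and use it only to define the per-protocol set.
2. State that poorly adherent participants, and those who stop medication for any reason, continue the scheduled CTs to month 24 or progression unless they withdraw consent, and stay in the full-analysis-set primary analysis.
3. Send sites a note to that effect. For anyone already withdrawn for adherence, and where consent permits, resume follow-up or retrieve CTs done under guideline surveillance.

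Which events should stop medication remains a matter for the investigators.

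**Cost.** A short protocol clarification, a site note and some retrieval effort. The remaining CTs are already scheduled, and no new visits, endpoint or sample size are needed.

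**Timing.** Assuming uniform accrual from June 2023, participants randomized in the first 29 months had finished 6 months of dosing by the end of April 2026. That is 589 × 29/31 = 551 if accrual ended in December 2025, or 589 × 29/35 = 488 if it ran to April 2026. Most adherence judgements have therefore probably been made, so the work is mainly resuming follow-up or retrieving scans for a group that may be empty. Scheduled scans already missed, and not done under usual care, cannot be recovered.
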